### Randomization

Participating clinicians are randomized 1:1 to either the TELESCOPE or EUC arm, with stratification based on primary practice affiliation at an RWJBH Primary Care Network or a Rutgers academic primary care practice site, and whether the clinician is a family medicine or internal medicine practitioner. Randomization of clinicians is done by the study’s biostatistician (SS) using STATA. After stratification, randomization is constructed within each stratum with random block sizes ranging from 2 to 6. We cannot blind clinicians or patient participants to the intervention. Patient participants are blinded to the study’s specific hypotheses; statisticians and outcome assessors are blinded to the allocation.

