### Patient Outcomes and Data Collection

After informed consent and enrollment into the trial, all patients complete a baseline survey (T0) and a follow-up survey 1 week after their scheduled clinic visit (T1). Surveys can be completed online, over the phone, or in-person. The study measures and timeline are summarized in Table 2.

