### Patient Surveys

The T0 patient survey assesses knowledge of LCS (using the validated LCS-12 measure^39^), decisional conflict (using the validated Decisional Conflict Scale^40^), cancer fatalism^41^, social norms about LCS^42^, medical mistrust^43^, perceived racial discrimination in healthcare^44,45^, health beliefs about LCS^46^, intentions to undergo LCS, and patients’ sociodemographic characteristics, health literacy, and medical history.

The T1 patient survey assesses the study’s primary outcome, the quality of the SDM process, using the SDM Process (SDMP_4) Scale which includes 4 items assessing whether there was a discussion of options, pros, cons, and preferences for LCS. ^47^ Also assessed at the T1 patient survey are knowledge of LCS, decisional conflict, preparation for decision making (using the validated PrepDM scale^48^), description of the LCS discussion with their clinician, LCS health beliefs, intentions to undergo LCS, and satisfaction with telehealth (for TELESCOPE arm patients) ^49^. In line with PRISM constructs (Table 3), the T1 patient survey also assesses TELESCOPE patients’ acceptability of the intervention (using the Ottawa Acceptability Measure^50^).

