### Patient Electronic Health Record (EHR) Reviews

A key secondary outcome is initial LCS uptake within 6 months after the decision coaching session (TELESCOPE) or the scheduled clinic visit date (EUC). Other secondary outcomes include adherence to annual LCS among those with an initial low-risk LDCT result by 18 months after the decision coaching session, tobacco treatment referral, receipt of tobacco treatment, and clinical outcomes, including diagnostic testing, cancer diagnoses, and treatment. For the TELESCOPE arm participants, data abstractions are conducted after the initial decision coaching session at 3 months (to trigger re-navigation for those who have not completed screening despite expressing a preference for it), 6 months (to assess initial LCS uptake, tobacco treatment referral/receipt, and clinical outcomes), 12 months (to assess follow-up testing in patients with Lung-RADS^®^ score of 3 or 4, tobacco treatment referral/receipt, and clinical outcomes^51^), and 18 months (to assess adherence to annual LCS, tobacco treatment referral/receipt, and clinical outcomes). For the EUC arm participants, data abstractions are conducted at 6, 12, and 18 months after their initial scheduled clinic visit for the same outcomes.

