### Data Management

All surveys are hosted on REDCap. To minimize missing data and non-compliance, staff review forms upon receipt to ensure that all items are completed and contact participants to determine if incomplete questions were deliberately skipped and/or to get a response.

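### The statement that statisticians and outcome assessors are blinded is not delivered by the procedures the protocol describes

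*Protocol article*

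**What the plan says.** The Randomization section makes three relevant statements. On who randomizes: "Randomization of clinicians is done by the study’s biostatistician". On patients and clinicians: "We cannot blind clinicians or patient participants to the intervention", although patients are kept unaware of the exact hypotheses. On everyone else: "statisticians and outcome assessors are blinded to the allocation".

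The outcome procedures come later:

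- **Primary outcome.** Under Patient Surveys: "The T1 patient survey assesses the study’s primary outcome, the quality of the SDM process, using the SDM Process (SDMP_4) Scale". The same survey includes "satisfaction with telehealth (for TELESCOPE arm patients" and an acceptability measure for that arm. Under Patient Outcomes and Data Collection: "Surveys can be completed online, over the phone, or in-person". Under Data Management, "staff review forms upon receipt to ensure that all items are completed and contact participants" about gaps.
- **EHR outcomes.** Under Patient Electronic Health Record (EHR) Reviews, for TELESCOPE: "data abstractions are conducted after the initial decision coaching session at 3 months (to trigger re-navigation", followed by abstractions at 6, 12 and 18 months. EUC has only the 6-, 12- and 18-month abstractions, counted from the scheduled visit. Table 2, note b, repeats the two time origins.

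**The concern.** The masking statement is one a reader uses to judge risk of bias, and it names two roles with no exception. If the described work shows those roles the arm, or if the outcome has no assessor other than an unblinded patient, the statement describes a trial better masked than the one being run.

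This affects the primary comparison, which rests on a subjective four-item patient report. It also affects the key secondary outcome, 6-month screening uptake, and the other outcomes taken from the EHR. For the EHR outcomes masking could largely be achieved, so an unsupported claim there is also a missed opportunity.

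**Working it through.** No arithmetic bears on this point. The sample-size figures are not inputs to it. The check sets the claim beside the procedures, role by role.

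**1. Statisticians.** Claim: blinded. Procedure: the study's biostatistician generates the clinician allocation. That person is therefore not blinded. The article describes no separate analyst and no coded arm labels. The Data Analysis section clusters by clinician, and clinicians are the randomized units. Someone who holds the allocation list could therefore recover the arm from clinician identity even with coded arms, unless clinician identifiers were also recoded. Result: the claim is false for the person who randomizes and undetermined for anyone else.

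**2. Assessor of the primary outcome.** Claim: blinded. Procedure: SDMP_4 is answered by the patient at T1, and patients are not blinded to the intervention. Result: the primary outcome has no blinded assessor. Staff handling does not supply one. The survey may be completed by phone or in person, it carries items meant only for TELESCOPE patients, and staff check returned forms and contact patients about gaps. Anyone handling a form that contains those items can see the arm.

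**3. EHR abstractors.** Claim: blinded. The procedures compare as follows.

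| Feature | TELESCOPE | EUC |
|---|---|---|
| Time origin | Initial coaching session | Scheduled clinic visit |
| 3-month abstraction | Yes, to trigger re-navigation | No |
| Origin of the LDCT order | Entered by a nurse navigator, signed by the clinician | Clinician |
| Coaching completion (Reach, Table 3) | Taken from ongoing EHR review | Not applicable |

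An abstractor who works from these definitions learns the arm from the start date alone. The chart may also show it through who entered the order. Result: the task as described reveals the arm, and no shielding is described.

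**The case against.** The strongest reply is that the open nature of the trial is already disclosed. The sentence on patients and clinicians comes shortly before the claim, and the article says plainly that SDMP_4 is in a patient survey. On this view, outcome assessors means the staff who collect or abstract data, and the statement concerns only them. This stands in part: nothing is hidden, and the open design is not at fault. But on that reading the statement gives no protection to the primary outcome, and the article does not say so.

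A second reply is that masking may be in place but undescribed. Another statistician may run the analysis, abstractors may be given only an index date, and different staff may do the 3-month check. Item order at T1 is not stated, and the article lists SDMP_4 ahead of the TELESCOPE-only measures, so a protective order may already be used. All of this is possible, and a condensed article may leave such details to the full protocol. It therefore cannot be said that every statistician and abstractor is in fact unmasked. What remains is that the article's positive statement conflicts with the steps it chose to describe.

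A reader might go further and infer that the false-positive rate is inflated by some amount, or that abstraction is biased toward the coached arm. The documents support neither. They give no bias size. Any figure would model reporting by patients who know what care they received, which cannot be avoided and which correcting the masking sentence would not change. LDCT uptake is a fairly objective record, and nothing shows the direction of any abstraction error.

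**Conclusion.** The point holds as a mismatch between the stated masking and the described procedures. It is certain for the primary outcome, which is self-reported by unblinded patients, and for the biostatistician who randomizes. For the EHR abstractors it is well supported but rests on an assumption: that they work from the arm-specific start dates and schedule as written, with no undescribed shielding.

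No numerical effect can be attached to it, and none is claimed. No test or sample size depends on it. It should be corrected because the statement bears on how the primary result will be judged, and because part of the missing masking can be obtained cheaply.

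**What to change.** 1. **Wording.** Limit the masking statement to the roles that are actually masked. State that the primary outcome is self-reported by unblinded patients.
2. **Statistician.** Have the primary analysis run by someone who did not generate the allocation, or drop statisticians from the claim.
3. **EHR abstraction.** Give outcome abstractors precomputed 6-, 12- and 18-month windows, without an arm label, from a date that exists in both arms, such as the scheduled visit or T0. Keep the 3-month re-navigation check separate from outcome abstraction. If the scheduled visit is the anchor, say how scans between T0 and the visit are counted, because coaching, and possibly the LDCT order, comes before the visit in TELESCOPE.
4. **T1 survey.** Ask SDMP_4 before any TELESCOPE-only items.

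**Cost.** No extra patients or visits are needed: only revised wording, a date field computed by the database and, if the order is not already so, a rearranged T1 form. The real downside is that a common date re-anchors the TELESCOPE uptake window after 134 patients had enrolled (Trial Status, early April 2024). It should be applied to all patients, including those already enrolled, from dates in the EHR, and recorded as an amendment. Chart clues such as navigator-placed orders will remain, so abstractor masking may be only partial and should be described that way. None of these steps removes reporting bias from patients who know their arm.

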### Description of Intervention

The TELESCOPE intervention involves patient and nurse navigators. The patient navigators (non-clinical) are from the RWJBH Navigation Program and help address patients’ barriers in accessing LCS. Patient navigators receive training (described below) to conduct telehealth LCS education and decision coaching sessions. Nurse navigators supervise patient navigators, place LDCT orders to be signed by clinicians for patients who elect screening, help patients overcome barriers (e.g., cost concerns, transportation, questions about insurance), and navigate patients with cancer or other abnormal findings.

### Intervention Materials

A team of decision scientists and LCS subject matter experts adapted decision coaching materials from a previous decision coaching intervention. ^27^ Adaptation included updating the scientific content to align with extant evidence and CMS guidelines, adding a script for patient navigation (addressing barriers to LCS and identifying screening locations), and adapting the language for primary care settings. The decision coaching materials include: (1) a 2-page **LCS Discussion Guide** with a summary of the benefits and harms of LCS and questions guiding patients in making a shared decision on LCS with their clinician; (2) a **Decision Coaching Manual,** which includes a script for the patient navigator to use during the decision coaching session; (3) **Decision Coaching Slides** which are used by the patient navigator during the session and serve as a visual aid for patients; and (4) **Frequently Asked Questions (FAQs)** to help patient navigators answer patients’ questions.

### TELESCOPE Intervention

Immediately after completing the baseline survey (T0), patients in the TELESCOPE arm are sent the 2-page LCS Discussion Guide and the Decision Coaching Slides via regular mail, and a link to the virtual meeting (Zoom or Microsoft Teams) at their preferred date and time. The decision coaching session is conducted over the phone with patients who do not have internet access. During the decision coaching session, patient navigators follow the scripted Decision Coaching Manual. The script begins with patient navigators introducing themselves and the purpose of the session, and then sharing their computer screen with patients to show the Decision Coaching Slides. Patient navigators review the slides’ content with the patient which includes lung cancer survival rates, importance of yearly LCS, how LCS is performed using an LDCT, potential benefits of LCS (finding lung cancer early and the magnitude of the benefit), and the potential harms of LCS (false alarms, need for additional testing, radiation exposure, overdiagnosis, and incidental findings).

After informing patients of the benefits and harms of LCS, the patient navigator stops sharing their screen and explores the patient’s thoughts about screening, barriers, and screening preferences. Patient navigators are trained in active listening techniques from motivational interviewing to ensure that the patient’s questions, barriers, and concerns are addressed. ^38^ If the patient indicates that she/he wants to be screened, the patient navigator helps identify the patient’s preferred screening location. If patients are unsure or do not want to be screened, the patient navigator advises them to discuss LCS and their concerns with their clinician at their upcoming clinic visit. Finally, the patient navigator assesses patients’ current smoking status, discusses the importance of not smoking, and offers to connect them with a Tobacco Treatment Program.

After the decision coaching session, the patient navigator alerts the nurse navigator to place an order for an LDCT for LCS, typically within 1 week of the patient indicating she/he wants to be screened. The LDCT order is reviewed and signed by the patient’s primary care clinician, typically within 24–48 hours. Nurse navigators follow up with the clinician if the order is not signed during this time period. Study staff reach out to imaging centers within 48 hours of the LDCT order being signed by the clinician to check if the LDCT order has been received and if they have contacted the patient about scheduling. Patients receive a follow-up call from a patient navigator if they have not scheduled their screening within 2 weeks, and a re-navigation call from a patient navigator if they have not completed screening within 3 months.

For TELESCOPE arm patients randomized to receive the decision coaching booster session, patient navigators follow the same process as the initial decision coaching session and a similar script to the Decision Coaching Manual. At the end of the booster session, patients are asked whether they want to pursue screening, and if the answer is yes, similar procedures as abovementioned are followed.

### Navigator Training and Fidelity

All patient navigators receive training on decision coaching, which includes: (1) a **1-hour didactic webinar** delivered on Zoom by two subject matter experts (a decision scientist and a clinician) who cover lung cancer epidemiology, what LCS and an LDCT is, LCS guidelines, the importance of SDM for LCS, and the importance of smoking cessation; (2) a **1-hour role-play session** which includes a 30-minute role-play exercise facilitated by a member of the research team in Zoom breakout rooms where patient navigators take turns using the Decision Coaching Manual with another navigator acting as the patient, followed by a 30-minute review of the role-play exercise by the research team; (3) **2 to 3 practice sessions** using the manual with a mock patient, with recordings of the practice sessions reviewed by the research team; and (4) a **1-hour group review session** on Zoom where the research team presents overall feedback from their review of the patient navigators’ practice session recordings. Once a patient navigator can deliver the decision coaching intervention with good fidelity, she/he starts conducting telehealth decision coaching sessions with patients. Patient navigators who need additional training are asked to conduct 1 to 4 additional practice sessions, reviewed by the research team, until they are able to deliver the script with good fidelity.

Intervention fidelity is evaluated by reviewing the first three decision coaching sessions by each navigator, followed by randomly selected 20% of each navigator’s remaining recorded sessions. We use a pilot-tested fidelity checklist to evaluate whether the scientific information presented is accurate and comprehensive, the navigator is capable of conducting the telehealth session over Zoom/Teams, and the navigator demonstrates good active listening skills. Two reviewers independently complete the fidelity checklist for each recording and conflicts in their ratings are resolved through discussion or adding a third reviewer.

The research team supports patient navigators with ongoing training by: (1) reviewing randomly selected recorded sessions from each patient navigator using the fidelity checklist and providing individual feedback via email; (2) conducting regular review sessions with navigators on Zoom (monthly in the first 6 months, and quarterly until recruitment is completed); (3) sending patient navigators a weekly knowledge check question (e.g., questions about LCS eligibility criteria, screening frequency) or check-in question (e.g., positive experiences or challenging aspects of navigating patients); and (4) conducting refresher training yearly or as needed.

### Enhanced Usual Care (EUC)

Patients in the EUC arm receive care by a clinician who is randomized to this study arm. EUC clinicians are responsible for discussing LCS, addressing the importance of smoking cessation, ordering the LDCT, and following up on the LDCT result with patients.

### Patient Outcomes and Data Collection

After informed consent and enrollment into the trial, all patients complete a baseline survey (T0) and a follow-up survey 1 week after their scheduled clinic visit (T1). Surveys can be completed online, over the phone, or in-person. The study measures and timeline are summarized in Table 2.

### Patient Surveys

The T0 patient survey assesses knowledge of LCS (using the validated LCS-12 measure^39^), decisional conflict (using the validated Decisional Conflict Scale^40^), cancer fatalism^41^, social norms about LCS^42^, medical mistrust^43^, perceived racial discrimination in healthcare^44,45^, health beliefs about LCS^46^, intentions to undergo LCS, and patients’ sociodemographic characteristics, health literacy, and medical history.

The T1 patient survey assesses the study’s primary outcome, the quality of the SDM process, using the SDM Process (SDMP_4) Scale which includes 4 items assessing whether there was a discussion of options, pros, cons, and preferences for LCS. ^47^ Also assessed at the T1 patient survey are knowledge of LCS, decisional conflict, preparation for decision making (using the validated PrepDM scale^48^), description of the LCS discussion with their clinician, LCS health beliefs, intentions to undergo LCS, and satisfaction with telehealth (for TELESCOPE arm patients) ^49^. In line with PRISM constructs (Table 3), the T1 patient survey also assesses TELESCOPE patients’ acceptability of the intervention (using the Ottawa Acceptability Measure^50^).

### Patient Electronic Health Record (EHR) Reviews

A key secondary outcome is initial LCS uptake within 6 months after the decision coaching session (TELESCOPE) or the scheduled clinic visit date (EUC). Other secondary outcomes include adherence to annual LCS among those with an initial low-risk LDCT result by 18 months after the decision coaching session, tobacco treatment referral, receipt of tobacco treatment, and clinical outcomes, including diagnostic testing, cancer diagnoses, and treatment. For the TELESCOPE arm participants, data abstractions are conducted after the initial decision coaching session at 3 months (to trigger re-navigation for those who have not completed screening despite expressing a preference for it), 6 months (to assess initial LCS uptake, tobacco treatment referral/receipt, and clinical outcomes), 12 months (to assess follow-up testing in patients with Lung-RADS^®^ score of 3 or 4, tobacco treatment referral/receipt, and clinical outcomes^51^), and 18 months (to assess adherence to annual LCS, tobacco treatment referral/receipt, and clinical outcomes). For the EUC arm participants, data abstractions are conducted at 6, 12, and 18 months after their initial scheduled clinic visit for the same outcomes.

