### Aims

The trial’s aims are to: (1) test the effectiveness of a decision coaching intervention for LCS delivered by patient navigators (TELESCOPE) versus EUC (enhanced usual care delivered by their primary care provider) on: a) quality of the SDM process about LCS (primary outcome); b) initial LCS uptake and subsequent adherence to annual LCS; and c) tobacco treatment referrals and receipt of tobacco treatment for current smokers; d) assess potential mediators and moderators of intervention effects; and (2) evaluate the implementation potential of patient navigator-delivered decision coaching for LCS by identifying organizational-, clinician-, and patient-level factors that might be barriers or facilitators to successful implementation.

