### Design

Figure 2 shows an overview of the TELESCOPE study design. We are conducting a cluster RCT with primary care clinicians as the unit of randomization into either (1) the TELESCOPE intervention arm, or (2) an EUC arm. Patients of clinicians in the TELESCOPE arm receive the decision coaching intervention delivered by trained patient navigators (hereafter referred to as ‘decision coaching session’) prior to an upcoming clinic visit with their primary care clinician. Patients of clinicians in the EUC arm have the opportunity to participate in an LCS discussion with their primary care clinician at an upcoming clinic visit. Usual care is enhanced by providing clinicians in both the TELESCOPE and EUC arms with access to a Continuing Medical Education (CME) webinar about LCS and an LCS discussion guide. Patients in the TELESCOPE arm who complete initial screening with negative or benign findings are due for their next screening in 12 months. Half of these participants are randomized to receive a telehealth decision coaching booster session with a patient navigator 1 month before their next annual screening. Table 1 provides a summary of components for the TELESCOPE and EUC arms, which are described in greater detail below.

For the TELESCOPE Trial, a community advisory board of diverse community stakeholders reviews and guides intervention development, recruitment strategies, study procedures, patient-facing materials (e.g., study flyers, informed consent forms, surveys, intervention materials), implementation (e.g., patient recruitment, retention, cultural acceptability), interpretation and dissemination of the results, and identification of next steps.

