## DISCUSSION

The goal of the TELESCOPE trial is to test a telehealth decision coaching intervention for LCS that can be implemented in real-world primary care settings serving racially, ethnically, and socioeconomically diverse patient populations. The TELESCOPE intervention involves patient navigators delivering a telehealth decision coaching session about LCS to screen-eligible patients prior to a primary care clinician visit. This novel approach has the potential to advance the implementation of SDM and improve guideline-concordant uptake of LCS by providing patients with high-quality decision support about LCS and decreasing the burden on busy primary care clinicians.

A strength of the trial is the recruitment of patient participants from a large integrated health system comprising a network of primary care sites across the state, including both community-based and academic sites, and institutional buy-in and collaboration from these sites. There is a growing trend of healthcare consolidation and it is estimated that 49% of primary care physicians and 72% of hospitals are affiliated with a large health system. ^64^ Hence, the results of this study may inform the development of scalable LCS interventions in other integrated health care systems. In addition, the mix of recruitment sites increases access to underserved minority and low-income participants, who have been underrepresented in LCS interventions thus far. Furthermore, the addition of a decision coaching booster session, conducted before the next annual screening is due for randomly selected patients, may improve adherence to annual LCS, which is crucial for reducing lung cancer mortality.

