**Figure 2 F2:**
[figure not shown]
Cluster Randomized Controlled Trial Design for TELESCOPE Trial.

**Table 1 T1:** Summary of the Study Components for the TELESCOPE and Enhanced Usual Care (EUC) Arms.

Participants	TELESCOPE Arm	EUC Arm
Clinicians	• Provided with access to CME webinar on lung cancer screening (LCS) and shared decision-making (SDM) • 2-page LCS Discussion Guide summarizing LCS eligibility, benefits/harms of LCS to consider, insurance coverage, and screening decisions	Same as TELESCOPE arm
Navigators	Navigator Pre-Intervention Training: • 1-hour live didactic webinar on LCS and SDM • 30-minute role play session using the decision coaching materials^a^ and 30-minute review of the role play session • 2–3 practice decision coaching sessions with mock patients • 1-hour group review of the practice sessions Navigator Ongoing Training: • Monthly review meetings with navigators in first 6 months, then quarterly meetings until recruitment is completed • Weekly knowledge check question • Yearly refresher training Intervention Fidelity: • Review of first 3 recorded coaching sessions using a fidelity checklist and thereafter randomly selected recordings; with individual feedback provided to each patient navigator	Not applicable (no EUC navigators)
Patients	Telehealth Decision Coaching Session: • Conducted on Zoom/Teams by patient navigator using decision coaching slides • Navigators provide information about the LDCT procedure, benefits and harms of LCS • Navigator assesses and address patient barriers • Navigator assesses screening preferences and places LDCT order if patient elects screening • Navigator offers referral for tobacco treatment to patients who are interested Follow-Up Navigation: • 2 weeks after order is placed and signed: Navigator follows up with patients who wanted to be screened but did not schedule the LDCT yet • 3 months after initial decision coaching session: Navigator re-navigates patients who wanted to be screened but did not complete LCS • Decision coaching booster session: 50% of patients who completed an initial LCS and have low-risk findings are randomly selected to receive a decision coaching booster session 1 month before their next annual screening is due	Clinic visit with EUC arm clinician: EUC clinicians are responsible for discussing LCS, addressing smoking cessation, ordering the LDCT, and following up on the LDCT result with patients.

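### The TELESCOPE-versus-EUC comparison of annual screening adherence is confined to patients with a low-risk first scan, a group that the intervention itself helps to form

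*Protocol article*

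**What the plan says.** The Aims section of the protocol article lists, among the outcomes on which TELESCOPE is tested against EUC, "initial LCS uptake and subsequent adherence to annual LCS". The section on electronic health record reviews places annual adherence among the other secondary outcomes and defines it as "adherence to annual LCS among those with an initial low-risk LDCT result by 18 months after the decision coaching session". For EUC patients, "data abstractions are conducted at 6, 12, and 18 months after their initial scheduled clinic visit for the same outcomes", so the outcome is collected in both arms.

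The Design section states: "We are conducting a cluster RCT with primary care clinicians as the unit of randomization". It also describes a second randomisation, in the TELESCOPE arm only, among patients whose first scan was negative or benign: "Half of these participants are randomized to receive a telehealth decision coaching booster session". Table 1 gives the same share: "50% of patients who completed an initial LCS and have low-risk findings are randomly selected to receive a decision coaching booster session". The Discussion says that the booster "may improve adherence to annual LCS, which is crucial for reducing lung cancer mortality".

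The Data Analysis section describes a between-arm comparison of screening uptake. It has no separate sentence on annual adherence or on how boosted and unboosted patients are handled. The intention-to-screen wording in the sample size section refers to uptake at 6 months.

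**The concern.** Clinicians are allocated before their patients are screened under the trial. In the TELESCOPE arm, coaching, order placement, a call to those who have not scheduled, and re-navigation at 3 months all act on whether a patient is screened. A patient enters the adherence denominator only after being screened with a low-risk result. The two subsets are therefore selected by different processes and need not have the same underlying tendency to return. A programme that gets more people through two annual scans could show a lower adherence percentage than EUC, or a higher one with no effect on returning.

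The booster adds a second difficulty. It targets this same outcome and exists in one arm only. Unless the analysis says which TELESCOPE strategy is compared with EUC, the arm's percentage has no single meaning.

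**Working it through.** **Inputs from the article (Sample Size and Power Calculation):** 210 patients per arm; uptake 14% (EUC) and 25.5% (TELESCOPE); ICC 0.04; type I error 5%, taken as two-sided; 420/120 = 3.5 patients per clinician. Booster share 50% (Design, Table 1). The article states no power or sample size for annual adherence.

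**1. The plan's own figure.** Design effect = 1 + (3.5 − 1) × 0.04 = 1.10; effective n = 210/1.10 = 190.9 per arm. Power for 14% versus 25.5% (pooled variance, no continuity correction) is 80.8%; with 4 or 3 patients per clinician it is 80.1% or 81.5%. The stated 80% is reproduced.

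**2. Size of the subset at those rates.** Screened: EUC 210 × 0.14 = 29.4; TELESCOPE 210 × 0.255 = 53.6. The article gives no low-risk share. Assuming 70% to 100%, the subsets are 21 to 29 (EUC) and 37 to 54 (TELESCOPE), with 19 to 27 in each booster half.

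**3. How far the subsets may differ.** Assume that every patient screened under EUC would also be screened under TELESCOPE. Then (25.5 − 14)/25.5 = 11.5/25.5 = 45% of screened TELESCOPE patients have no counterpart in the EUC subset.

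**4. Illustration with no intervention effect on returning.** All adherence rates here are assumed, with the same low-risk share throughout. Patients screened in either arm adhere at 60%; those screened only because of TELESCOPE adhere at rate b. The TELESCOPE subset rate is (0.14 × 0.60 + 0.115 × b)/0.255. Over all enrolled patients, before multiplying both arms by the low-risk share, the rates are 0.14 × 0.60 for EUC and 0.14 × 0.60 + 0.115 × b for TELESCOPE.

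| b | Subset: EUC | Subset: TELESCOPE | Difference (points) | All enrolled: EUC | All enrolled: TELESCOPE |
|---|---|---|---|---|---|
| 30% | 60% | 46.5% | −13.5 | 8.4% | 11.9% |
| 50% | 60% | 55.5% | −4.5 | 8.4% | 14.2% |
| 60% | 60% | 60.0% | 0 | 8.4% | 15.3% |
| 70% | 60% | 64.5% | +4.5 | 8.4% | 16.5% |

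The subset contrast can thus be negative, zero or positive although nothing acts on returning.

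**5. Booster, if the halves are pooled.** With unboosted adherence r and a booster effect of x points, the TELESCOPE subset rate is 0.5 × r + 0.5 × (r + x) = r + x/2. An assumed x of 20 points moves the subset rate by 10. Over all enrolled patients the shift is 0.255 × low-risk share × x/2, or 2.0 to 2.3 points for a share of 80% to 90%. Changing the denominator therefore shrinks the shift but does not remove it.

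**The case against.** There is a good clinical reason for the denominator. The article treats patients with a negative or benign first scan as due again at 12 months and follows Lung-RADS 3 or 4 results separately. Adherence to an annual scan applies only to people due for one. This stands: the subset rate is a legitimate descriptive measure, and the difficulty lies only in reading its difference between arms as an effect of the intervention.

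A reader might infer that the plan pools boosted and unboosted patients against EUC. The article does not say so, and its analysis section is silent; an unseen analysis plan may settle it. Pooling is one possible handling, not the stated one.

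A reader might also infer that the bias runs against TELESCOPE because EUC screeners are more self-motivated. That is conjecture. EUC clinicians also have the webinar and discussion guide, and the article has no data on who returns.

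Nor is it supported to fault the booster comparison as underpowered. It is a fresh randomisation and valid within its subset; no power is claimed for it, and the Discussion is hedged. It will be imprecise if uptake is near the rates above, but actual uptake may be higher.

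Finally, the all-enrolled proportion does not isolate repeat adherence. In the table it favours TELESCOPE even with no effect on returning, because more patients are screened in the first place. This is a real limitation and belongs in the report.

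**Conclusion.** The concern holds for the arm contrast. The article makes annual adherence a TELESCOPE-versus-EUC outcome and fixes its denominator on an event after randomisation that the intervention is meant to change. An analysis plan that follows this text inherits the problem. At the uptake rates used for power, about 29 and 54 patients would be screened, and 45% of the latter would have no EUC counterpart if everyone screened under EUC would also be screened under TELESCOPE. The size and direction of any distortion are unknown; the −13.5 to +4.5 points above depend on assumed adherence rates, and the distortion is zero if both kinds of patient return equally often.

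On the booster, the supported statement is narrower: the article does not say how boosted patients enter the arm contrast, and pooling would shift the TELESCOPE subset rate by half the booster effect.

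This should be fixed, but it is not critical. It concerns a lower-tier secondary outcome. The primary comparison of the shared decision-making score and the key secondary comparison of 6-month uptake do not depend on it.

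**What to change.** - Define the between-arm estimate as the proportion of all enrolled patients who complete both an initial scan and the annual scan by 18 months. State that patients with Lung-RADS 3 or 4 results stay in the denominator and that their follow-up is reported separately; counting that follow-up as success would change the outcome definition.
- Report the adherence rate in the low-risk subset by arm beside it, labelled descriptive and not a randomised comparison.
- For TELESCOPE without booster versus EUC, give booster-eligible patients allocated to no booster weight 2, those allocated to booster weight 0, and all other TELESCOPE patients weight 1. Reverse the first two weights for TELESCOPE with booster. This is valid because booster allocation is random at 50%. Use standard errors that allow for the weights and for clustering by clinician.
- Report booster versus no booster as its own randomised, exploratory contrast with a confidence interval.

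**Cost.** The records needed are already abstracted, and recruitment is expected to run to May 2026, so the change can be made in the text before outcomes are complete. The all-enrolled proportion is lower and less familiar than an adherence rate, and it combines initial uptake with returning.

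The weighting also costs some precision. Take an assumed 85% low-risk share and 50% adherence in both arms, ignoring clustering. The eligible share e of TELESCOPE is 0.255 × 0.85 = 0.217 and the all-enrolled rates are 10.8% and 6.0%. Times 210, the variances are 0.0966 (TELESCOPE unweighted, p(1 − p)), 0.1508 (TELESCOPE weighted, 2 × e × 0.25 + 0.25 × e × (1 − e)) and 0.0560 (EUC). The 95% CI half-width for the difference goes from 1.96 × √(0.1526/210) = 5.3 points to 1.96 × √(0.2068/210) = 6.2 points, about 16% wider.
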